# The Potential of Normobaric Oxygen Therapy to Enhance Erythropoiesis, Reduce Oxidative Stress, and Modulate Immune Function in Colorectal Cancer Patients Undergoing Chemotherapy: Study Protocol for a Prospective, Randomized, Double-Blind, Placebo-Controlled Trial (NBO-ONCO)

**DOI:** 10.3390/jcm14145057

**Published:** 2025-07-17

**Keywords:** colorectal cancer (CRC), normobaric oxygen therapy (NBO), chemotherapy-induced anemia, oxidative stress, immune modulation, erythropoiesis, supportive cancer care, adverse effects, stress, anxiety, depression, psychological well-being, quality of life

## Abstract

Colorectal cancer is a major global health challenge, and patients undergoing chemotherapy often experience anemia, immune dysfunction, and oxidative stress, which can negatively affect treatment outcomes and quality of life. A simple and non-invasive approach like normobaric oxygen therapy may help by boosting red blood cell production, reducing inflammation, and strengthening the immune system. This study aims to evaluate its effectiveness in patients with colorectal cancer receiving chemotherapy, assessing its impact on erythropoiesis, immune function, oxidative stress, and psychological well-being. By exploring this potential therapy, we hope to uncover a safer and more accessible way to support cancer patients during treatment with chemotherapy. If proven beneficial, normobaric oxygen therapy could be integrated into oncology treatment protocols, enhancing patient outcomes and supporting overall quality of life.

## 1. Introduction

Colorectal cancer (CRC) is the third most commonly diagnosed cancer worldwide and the second leading cause of cancer-related deaths, accounting for over 1.9 million new cases and 935,000 deaths in 2020 [1]. The incidence of CRC is highest in developed countries, largely due to dietary and lifestyle factors such as high consumption of processed foods, red meats, and alcohol and physical inactivity [2]. According to the Global Cancer Observatory, CRC cases are expected to rise sharply by 2035, particularly in low to middle-income countries adopting Westernized diets [3].

The increasing incidence in these regions underscores the impact of lifestyle changes and the urgent need for preventive strategies [4]. CRC screening programs have successfully reduced mortality rates in developed nations by enabling the early detection and removal of precancerous polyps [5]. For instance, widespread colonoscopy screening in the United States has led to a significant decline in CRC incidence and mortality [6]. However, limited access to screening in developing countries contributes to diagnoses at more advanced stages, resulting in poorer outcomes [7].

Economically, CRC imposes substantial healthcare costs. Advanced cases requiring treatments such as chemotherapy, targeted therapies, and surgical interventions like liver resections place a significant financial burden on healthcare systems [8]. In Europe, the total annual cost of CRC care was estimated at EUR 19.1 billion in 2015 [9]. These costs highlight the importance of implementing cost-effective screening programs globally to detect precancerous lesions early and reduce the economic strain [10]. In Poland, CRC remains one of the most prevalent cancers, ranking as a leading cause of cancer mortality [11].

In 2018, Poland reported approximately 18,000 new CRC cases, with over 10,000 cases among men and about 8000 among women [12]. Mortality rates are substantial, contributing significantly to the nation’s cancer burden [13]. Given the substantial impact of CRC on public health, there is a pressing need for innovative supportive therapies, such as normobaric oxygen (NBO) therapy, to improve patient-reported outcomes and address treatment-related complications.

NBO therapy involves delivering oxygen at atmospheric pressure but at a higher fraction than the ~21% found in ambient air. In contrast, hyperbaric oxygen therapy (HBOT) uses both an elevated oxygen concentration and increased atmospheric pressure (typically ≥1.4 ATA), necessitating specialized pressurized chambers [14]. While HBOT has been studied extensively for conditions such as radiation-induced tissue damage, diabetic foot ulcers, and wound healing, NBO offers a more accessible alternative with fewer risks (e.g., lower incidence of barotrauma, reduced logistical constraints) and may be easier to implement in a variety of clinical settings [15]. Mechanistically, NBO may support erythropoiesis, reduce oxidative stress, and modulate immune function through several pathways. First, by delivering a higher oxygen fraction at normobaric pressure, NBO can alleviate tissue hypoxia—including in the kidneys—which may help preserve or enhance endogenous erythropoietin (EPO) production [16]. Second, the improved oxygenation can potentially reduce the generation of reactive oxygen species (ROS) by optimizing mitochondrial function, thereby attenuating oxidative stress and cellular damage [17]. Third, improved oxygen availability in tissues has been hypothesized to counteract tumor hypoxia, which can otherwise promote immunosuppressive mechanisms (e.g., upregulation of immune checkpoint molecules and recruitment of myeloid-derived suppressor cells) [18,19]. Consequently, NBO could restore or enhance immune cell functionality, potentially improving the anti-tumor immune response in cancer patients [20,21,22].

Recent research has explored the potential benefits of NBO in various medical conditions, including its role in supporting erythropoiesis, reducing oxidative stress, modulating immune function, and improving stress, emotional well-being, and cognitive functions in patients [23].

Anemia is a common complication in cancer patients undergoing chemotherapy, often due to myelosuppression, where the bone marrow’s ability to produce blood cells is suppressed by cytotoxic agents, and reduced EPO production due to kidney damage [16]. EPO is a glycoprotein hormone primarily produced by the kidneys, which stimulates red blood cell formation (erythropoiesis) in the bone marrow. NBO may enhance erythropoiesis under hypoxia conditions by increasing oxygen availability, thereby improving kidney oxygenation and stimulating EPO synthesis [24]. NBO leads to a reduction in oxidative stress in the kidneys that may cause less chemotherapy-induced damage to the kidney parenchyma and thus ensure the viability of EPO-producing cells [25,26]. Hypoxia plays a key role in both normal and pathological cellular processes, influencing EPO gene expression. Extracellular superoxide dismutase (EC-SOD) has been identified as a critical regulator of this response, acting to suppress hypoxia-induced EPO expression. This suggests that superoxide functions as a signaling molecule in the regulation of EPO production, with its downstream effects partially mediated by hypoxia-inducible factor 1-alpha (HIF-1α) [17].

Over the past decade, concerns have grown about the risks of transfusions associated with cancer treatment. Furthermore, no clear evidence has arisen about the benefits of transfusion and questions about increasing mortality have even been raised. The use of a red blood cell progenitor enhancer such as exogenous EPO is extensively recognized, and a relatively low rate of adverse effects has been reported in patients adequately followed in medical institutions. However, the price of such medications is very high and their availability is limited in some countries. A recently described phenomenon called the ‘normobaric oxygen paradox’ (NOP) may show possible clinical applications [27].

Cancer patients often experience significant psychological stress, emotional disturbances, and cognitive impairments due to the disease itself and the side effects of chemotherapy [28]. NBO has shown potential in improving cognitive functions and emotional well-being, which could enhance the overall quality of life for these patients. A preliminary study by Kujawski et al. [29] investigated the effect of NBO on cognitive function in healthy adults. The study demonstrated that NBO sessions led to significant improvements in attention, memory, and executive functions compared with the control group.

These findings suggest that NBO may enhance neural activity and cerebral oxygenation, leading to better cognitive performance. Psychological stress and mood disorders such as depression are common in cancer patients [30]. Bloch et al. [31] conducted a randomized, double-blind, proof-of-concept trial examining the effects of NBO treatment on individuals with mild-to-moderate depression. The study found that NBO significantly reduced depressive symptoms compared with the placebo group. The authors suggested that increased oxygen availability might influence neurotransmitter systems involved in mood regulation, such as serotonin and dopamine pathways.

Reducing stress is a key element supporting cancer treatment, and normobaric therapy can play a significant role. Reduced stress levels improve the function of the immune system. Cortisol can inhibit the activity of some immune cells, so its neutralization, thanks to normobaric therapy, can accelerate the treatment process. The introduction of endorphins and improved mood, as well as general well-being, can significantly increase patients’ motivation to continue mobilizing in treatment. A proper hormonal balance resulting from normobaric therapy contributes to reducing the risk of stress-related complications.

It was revealed that NBO interventions can be effective in supporting mental health. Bloch et al. [32] conducted a pilot study exploring normobaric hyperoxia treatment in patients with schizophrenia. The study administered NBO sessions to patients with schizophrenia and observed improvements in negative symptoms such as blunted affect, social withdrawal, and apathy. Additionally, enhancements in cognitive deficits were noted, particularly in areas like attention, executive functioning, and working memory. These findings indicate that NBO could modulate neural processes underlying schizophrenia, potentially by enhancing cerebral oxygenation and influencing neurotransmitter systems implicated in the disorder. The study suggests that NBO may offer a novel adjunctive treatment modality for schizophrenia, addressing symptoms that are often resistant to conventional therapies [33,34,35].

While HBOT has been extensively studied in oncology, particularly for its benefits in managing radiation-induced tissue injuries and promoting wound healing [36], NBO presents a safer and more accessible alternative, with fewer risks associated with high-pressure exposure [37]. NBO’s potential to improve anemia, reduce oxidative stress, modulate immune function, and enhance cognitive and emotional well-being could synergistically enhance the effectiveness of chemotherapy and improve patient outcomes. Further clinical trials are needed to establish standardized protocols and confirm the efficacy of NBO as a supportive therapy in cancer care. Therefore, this gap in the literature underscores the need for a well-designed, randomized, placebo-controlled trial to systematically evaluate NBO’s impact on anemia, oxidative stress, immune modulation, and psychological well-being in CRC patients undergoing chemotherapy.

The following primary objectives were selected: First, to evaluate the efficacy of NBO in reducing anemia in CRC patients undergoing chemotherapy by measuring markers of erythropoiesis, such as EPO levels, HIF-1α, and complete blood counts. Second, to evaluate the effect of NBO on reducing oxidative stress and improving patients’ cognitive and emotional functions by analyzing levels of cortisol, GABA, dopamine, and other indicators of allostatic load. Third, to analyze the effects of NBO on immune system parameters and reduction in oxidative stress by evaluating a panel of 24 serum cytokines and TNFα levels. Fourth, to identify genetic markers of response to NBO therapy by analyzing the secretome to investigate molecular changes and profiles related to immune function and response to treatment. The effects of NBO on improving patients’ cognitive and emotional functions were quantified simultaneously in the same clinical specimen. In turn, a secondary objective is to assess the impact of NBO on patient-reported outcome measures (PROMs) using standardized tools such as the Perceived Stress Questionnaire (PSQ), Hospital Anxiety and Depression Scale (HADS), and Euro-Quality of Life Questionnaire (EQ-5D).

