### 2.4. Eligibility Criteria

Inclusion criteria: (1) age between 18 and 80 years (participants must be adults); (2) diagnosed with CRC (stage II–IV, scheduled for standard chemotherapy (for the study and control groups); (3) baseline hemoglobin levels above 10 g/dL; (4) no concurrent hematologic malignancies; (5) an eastern Cooperative Oncology Group (ECOG) performance status of 0–2 (ensuring that participants are ambulatory and capable of self-care); (6) a life expectancy of at least 12 months (participants are expected to survive for the duration of the study); (7) the ability and a willingness to comply with all study procedures and schedules (including NBO therapy sessions and follow-up visits); (8) adequate organ function as determined by laboratory tests (liver function tests (ALT, AST) and renal function tests (serum creatinine, eGFR)); (9) women of childbearing potential must have had a negative pregnancy test prior to enrollment and agreed to use effective contraception during the study (to ensure safety for potential pregnancies); and (10) written informed consent was obtained prior to any study-related procedures (participants must understand and agree to all aspects of the study).

Exclusion criteria: (1) age under 18 years or over 80 years; (2) severe cardiovascular or respiratory conditions (e.g., unstable angina, recent myocardial infarction, advanced COPD); (3) severe anemia (hemoglobin < 10 g/dL) or any hemolytic disorder that could confound study outcomes; (4) uncontrolled diabetes mellitus (e.g., HbA1c > 8.0% or poor glycemic control requiring frequent hospitalizations); (5) pregnancy or breastfeeding; (6) severe infection or immunocompromised status unrelated to cancer (e.g., advanced HIV infection); (7) current psychiatric or neurological disorders that could interfere with study participation; (8) participation in other investigational therapies within the last 30 days; (9) a lack of written informed consent for study participation; (10) autoimmune or inflammatory conditions (e.g., lupus, rheumatoid arthritis on immunosuppressive therapy) that significantly alter immune responses; and (11) the presence of any contraindication for NBO therapy (e.g., active bleeding, acute infections, inflammation of the optic nerve, epilepsy or seizures, uncontrolled diabetes as noted above, pneumothorax, emphysema, electronic implants).

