### 2.5. Randomization and Blinding

Participants will be randomized in a 1:1 ratio to the active NBO (study) or placebo NBO (control) group using a stratified randomization method. Stratification factors include CRC stage (II vs. III vs. IV) and baseline hemoglobin levels (<12 g/dL vs. ≥12 g/dL), as these variables can significantly influence treatment outcomes and the incidence of anemia. A computer-generated allocation sequence will be used within each stratum to ensure an even distribution of these characteristics across the two study arms. Only the NBO operators (who are not involved in data collection or analysis) will have access to the allocation list to administer the assigned intervention. All other study personnel and participants will remain blinded to group assignments.

Patients and clinical staff (excluding NBO operators who administer the therapy) will be blinded to the treatment allocations. Placebo NBO sessions mimic active NBO conditions without therapeutic oxygen adjustments. Both patients and clinical staff involved in patient care and data collection will be blinded to the treatment allocations. NBO operators who administer the therapy will not be blinded in order to ensure the correct delivery of the intervention. They will be trained to maintain confidentiality and avoid any disclosures that could compromise blinding. Both active NBO and placebo NBO sessions will be conducted in chambers that are identical in appearance and setup. This includes similar equipment, procedures, and environmental conditions in order to prevent patients and blinded staff from discerning group assignments.

Unblinding will occur after the database is locked and completion of statistical analysis. Immediate unblinding is permissible in medical emergencies where treatment knowledge is essential for patient care. Unblinding may occur immediately if a serious adverse event or medical emergency arises where knowledge of the treatment allocation is essential for the patient’s safe and effective management. The decision to unblind in an emergency will be made by the principal investigator or a designated medical officer.

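### Objective 1, reducing anemia, does not separate improving existing anemia from limiting chemotherapy-induced anemia, and the single pooled comparison mixes the two

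*Protocol article*

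**What the plan says.** The Introduction gives the first primary objective as "to evaluate the efficacy of NBO in reducing anemia in CRC patients undergoing chemotherapy", to be assessed "by measuring markers of erythropoiesis, such as EPO levels, HIF-1α, and complete blood counts". No definition of anemia, anemia event or responder criterion goes with it.

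Section 2.4 includes patients with "baseline hemoglobin levels above 10 g/dL" who are "scheduled for standard chemotherapy", and excludes "severe anemia (hemoglobin < 10 g/dL) or any hemolytic disorder that could confound study outcomes". There is no upper hemoglobin limit, and neither anemia nor low oxygen saturation is required.

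Section 2.5 stratifies randomization by CRC stage and by "baseline hemoglobin levels (<12 g/dL vs. ≥12 g/dL" (closing bracket omitted), and justifies both factors "as these variables can significantly influence treatment outcomes and the incidence of anemia".

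Section 2.10 names the Mann–Whitney U test for intervention against control and does not mention the strata. The sample size is built on an assumed 40% difference in an erythropoiesis measure, with EPO as the example.

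**The concern.** A patient who enters with a hemoglobin of, say, 14.5 g/dL meets the hemoglobin criterion but has no anemia that could be reduced. The most the treatment can do for that patient is limit a fall during chemotherapy. A patient who enters just above 10 g/dL could show either an improvement or a smaller fall. These are two questions, and the objective's wording covers both without choosing.

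Two consequences follow for the pooled comparison:

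- **Interpretation.** A difference in EPO or blood counts that arises in patients who were never anemic could be reported under the heading of reduced anemia.
- **Dilution.** If the effect depends on baseline hemoglobin, the pooled estimate averages a larger and a smaller effect. The sample size makes no allowance for this. The protocol's rationale gives some reason to consider it, since the Introduction says "NBO may enhance erythropoiesis under hypoxia conditions by increasing oxygen availability", while entry does not select for hypoxia.

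**Working it through.** **Reading the passages together**

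| Element | Existing anemia | Anemia arising on study |
|---|---|---|
| Objective 1 (Introduction) | reducing anemia | not excluded |
| Entry (2.4) | hemoglobin above 10 g/dL, no ceiling, anemia not required | patients scheduled for chemotherapy |
| Strata (2.5) | split at 12 g/dL | justified by incidence of anemia |
| Mechanism (Introduction) | effect under hypoxia | less chemotherapy damage to the kidney |

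Both readings have support, and nothing in the text settles which one the objective means.

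**The plan's own figure.** Section 2.10 gives 127 per group, two-sided alpha 0.05, power 80%, 1:1 allocation, a two-sample t-test and 30% dropout. It states neither d nor an SD, so 127 cannot be reproduced uniquely:

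- d = 0.40: 100 per arm by t-test; 100/0.7 = 143 (no match) and 100 × 1.3 = 130 (close, but dropout should be allowed for by division).
- d = 0.425: 88 per arm; 88/0.7 = 126 (close).

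Working backwards, 127 × 0.7 = 88.9, about 89 evaluable per arm. At that size, 80% power corresponds to d = 0.422.

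**Possible dilution (illustration).** Let f be the share of patients below 12 g/dL. The protocol does not give it, so f = 0.3, 0.5 and 0.7 are assumed. Also assumed are d = 0.422 below 12 g/dL, no effect at or above 12 g/dL, equal SD in both strata and the same share in each arm. Then:

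- pooled effect = f × d, tested with 89 per arm;
- lower stratum alone: d tested with about 89 × f per arm;
- interaction: z = d / √(2/n₁ + 2/n₂), power ≈ Φ(z − 1.96).

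| f | Pooled effect | Pooled power | n per arm below 12 | Power, lower stratum alone | Interaction z | Interaction power |
|---|---|---|---|---|---|---|
| 0.3 | 0.127 | 13% | 27 | 33% | 1.29 | 25% |
| 0.5 | 0.211 | 29% | 44 | 50% | 1.41 | 29% |
| 0.7 | 0.295 | 50% | 62 | 65% | 1.29 | 25% |

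For example, at f = 0.5: √(2/44 + 2/45) = 0.300, and 0.422/0.300 = 1.41.

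**A milder case.** If patients at or above 12 g/dL have half the effect, the pooled effect is d × (f + 0.5(1 − f)). This gives 0.274, 0.317 and 0.359, with power 44%, 56% and 66%. With the same effect in both strata there is no dilution and power is 80%.

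**The case against.** The strongest reply is that the protocol is about anemia caused by chemotherapy. Section 2.3 describes anemia as a side effect of chemotherapy, patients enter before or around its start, and the strata are justified by the incidence of anemia. On that reading a patient without anemia at entry is a proper subject: hemoglobin can fall on study, and limiting that fall reduces anemia. The listed markers can be measured in everyone. The Introduction also gives a protective route, less chemotherapy damage to EPO-producing kidney tissue, which needs neither baseline anemia nor low saturation. All of this stands, and it is why the repair below takes this reading as the main one.

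A reader might go further and infer that the pooled comparison cannot answer the objective, that only patients between 10 and 12 g/dL can show a benefit, or that many patients fall outside the objective. The documents do not support this. The randomized contrast is valid for the population enrolled. Patients at or above 12 g/dL can develop anemia later. The 12 g/dL value is a stratification cut, not a stated definition of anemia, and no share on either side of it is given.

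It is also fair to say that subgroup and stratified analyses are often left to the SAP, which is not shown, and that section 2.10 promises sensitivity analyses. Their absence from the article is therefore not the point. The point is that the stated objective does not say which question is asked of the stated population.

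Finally, the power figures use a d back-solved from a sample size exemplified by EPO, and the first table takes the extreme case of no effect at or above 12 g/dL. They show what could happen, not what is expected.

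**Conclusion.** The concern holds as one of wording and interpretation. Objective 1 does not distinguish improving existing anemia from limiting anemia during chemotherapy, in a population with a hemoglobin floor, no ceiling and a planned stratum at or above 12 g/dL. The pooled Mann–Whitney comparison is valid but mixes the two questions, and as worded a marker difference in non-anemic patients could be reported as reduced anemia.

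Dilution is possible but cannot be sized from the protocol. Under the assumptions stated above, power at the detectable effect ranges from 80% (same effect in both strata) to 13% (30% of patients below 12 g/dL, no effect in the rest). The point should be settled before the first participant is enrolled, planned for March 2026, but it does not call the design into question.

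**What to change.** 1. Reword objective 1, for example: *to evaluate whether NBO limits the fall in hemoglobin and the incidence of anemia during chemotherapy in all randomized patients*. State the definition of anemia, and say how patients who already meet it at V1 are counted.
2. Analyse the hemoglobin comparison at V3 with the existing <12/≥12 g/dL stratum in the model, or with a stratified rank test if a rank method is kept.
3. Report the treatment effect within each stratum, with a treatment-by-stratum term, as a pre-specified supportive analysis.
4. Let any statement about improving existing anemia refer to the lower stratum's estimate, and label it supportive. The main conclusion should not be made to depend on that stratum: under the first set of assumptions above its power is only 33% to 65%.

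**Cost.** Changes to the wording of the objective and the analysis only. The strata exist, and blood counts are taken at V1 to V5. Eligibility and sample size stay unchanged. The downsides are imprecise stratum estimates, an interaction term with low power (about 25% to 29% in the illustration), and a more modest claim from the pooled result.

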#### 2.8.2. STRESS Package

This set captures markers related to oxidative stress, hormonal response, and physiological load, including: (1) ROS (measures reactive oxygen species levels); (2) cortisol, GABA, Dopamine, and Serotonin (stress hormones and neurotransmitters); (3) allostatic load (CRP, fibrinogen, HbA1c, DHEA-S, blood pressure (SBP, DBP), and heart rate (HR), to assess chronic stress burden); and (4) anthropometry (BMI, BSA, and WHR, reflecting body composition and risk).

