## 5. Conclusions

Chemotherapy-induced anemia, oxidative stress, and immune suppression remain major obstacles in CRC management, often reducing treatment tolerability and quality of life. NBO therapy represents a non-invasive, accessible intervention with the potential to bolster erythropoiesis, mitigate oxidative stress, modulate immune responses, and enhance psychological well-being. By improving oxygen availability, NBO could also help downregulate hypoxia-induced immunosuppression and potentially increase the efficacy of immunotherapy. The resulting improvements in neuronal energy processes and mood regulation further suggest benefits for cognitive and emotional function. If proven effective, NBO could become an important adjunctive therapy in CRC, alleviating treatment-related side effects, improving patient outcomes, and reducing the overall burden on healthcare systems.

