## Figures and Tables

**Figure 1 jcm-14-05057-f001:**
[figure not shown]
Flow diagram of the study course.

**Table 1 jcm-14-05057-t001:** Research plan.

Visit	Phase	Assessments
V0	Prequalification (screening)	Consent, patient history, baseline data
V1	Randomization and pre-test	ANEMIA, STRESS, IMMUNE, GENETIC, PROMs + BIOBANK
NBO sessions 1–5		NBO intervention (first five weeks)
V2	Midpoint evaluation	ANEMIA, STRESS, IMMUNE, GENETIC, PROMs
NBO sessions 6–10		NBO intervention (second five weeks)
V3	Finalization and post-test	ANEMIA, STRESS, IMMUNE, GENETIC, PROMs
V4	3 month follow-up	ANEMIA, STRESS, IMMUNE, GENETIC, PROMs
V5	6 month follow-up	ANEMIA, STRESS, IMMUNE, GENETIC, PROMs

Abbreviations: NBO, normobaric oxygen intervention; V, visit; I, Intervention; ANEMIA, assessment of erythropoiesis markers; STRESS, assessment of stress and oxidative stress; IMMUNO, immunological parameter assessment; GENETIC, analysis of the secretome and molecular changes; PROMs, patient-reported measure outcomes; BIOBANK, collection of human biological material (blood samples) in accordance with the Quality Standards for Polish Biobanks v. 2.00 (2021).

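### Primary objective 2 includes cognitive function, but the plan contains no measure of cognition and names hormone, neurotransmitter and allostatic-load markers in its place

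*Protocol article*

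**What the plan says.** The last paragraph of section 1 of the protocol article lists four primary objectives. The second joins three things: oxidative stress, cognitive function and emotional function. It also fixes how they are to be evaluated: "cognitive and emotional functions by analyzing levels of cortisol, GABA, dopamine, and other indicators of allostatic load". After the fourth objective, the paragraph returns to the subject: "The effects of NBO on improving patients’ cognitive and emotional functions were quantified simultaneously in the same clinical specimen".

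The secondary objective in the same paragraph covers patient-reported outcomes, using "standardized tools such as the Perceived Stress Questionnaire (PSQ), Hospital Anxiety and Depression Scale (HADS), and Euro-Quality of Life Questionnaire (EQ-5D").

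Section 2.8.2 describes the STRESS package, the primary-outcome set that serves objective 2: "This set captures markers related to oxidative stress, hormonal response, and physiological load". It classes the four analytes as "cortisol, GABA, Dopamine, and Serotonin (stress hormones and neurotransmitters"). In Table 1, each of the visits V1 to V5 carries the same set, "ANEMIA, STRESS, IMMUNE, GENETIC, PROMs", with biobanking added at V1. V0 covers consent, history and baseline data.

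**The concern.** An objective should name a quantity that the trial measures. Here the stated quantity is cognitive function, and the stated means is a set of hormone, neurotransmitter and physiological markers. A treatment difference in cortisol, GABA or dopamine would show a difference in those analytes. It would not show that attention, memory or executive function had improved. Equally, no difference in the analytes would not show that cognition was unchanged.

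What is at stake is the scope of a primary-level claim. This is separate from multiplicity and from the choice of test: no division of alpha and no analysis model turns a marker into a measurement of cognition. Nor is it a detail that an article would leave to a fuller protocol or an analysis plan, because the article itself names the measure, and that measure does not fit the construct.

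**Working it through.** The plan gives no figure on this point to reproduce. The check is a comparison of the constructs in objective 2 with everything the plan collects.

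**Step 1. What cognition means in this article.** The rationale in section 1 cites a study in healthy adults that reported gains in attention, memory and executive function, and a pilot study in schizophrenia that noted gains in similar domains. The article therefore treats cognition as performance in such domains.

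**Step 2. What is collected.**

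| Source (protocol article) | Content | Cognitive measure? |
|---|---|---|
| 2.8.1 ANEMIA | Erythropoiesis, blood count, renal, hepatic, metabolic, iron and inflammation markers | No |
| 2.8.2 STRESS | ROS, cortisol, GABA, dopamine, serotonin, allostatic-load components, anthropometry | No |
| 2.8.3 IMMUNO | Multiplex cytokine panel | No |
| 2.8.3 and Table 1, GENETICS | Secretome and molecular changes | No |
| 2.9.1 PSQ | Stress, 30 items | No |
| 2.9.2 HADS | Anxiety (7 items) and depression (7 items) | No |
| 2.9.3 EQ-5D | Mobility, self-care, usual activities, pain/discomfort, anxiety/depression | No |

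Count: 0 of 4 laboratory packages and 0 of 3 questionnaires.

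**Step 3. When it is collected.** Section 2.7 and Table 1 give six visits. V1 to V5 carry only the packages above (plus biobanking at V1), and V0 carries no outcome assessment of this kind. Count: 0 of 6 visits.

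**Step 4. Objective 2, part by part.**

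- Oxidative stress: measured, by ROS in the STRESS package.
- Allostatic load: measured; its components are listed in section 2.8.2.
- Emotional function: measured directly by HADS and PSQ (and by one EQ-5D domain), but as secondary outcomes.
- Cognitive function: not measured.

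**Step 5. Objective against reporting plan.** Section 3 lists as primary results the changes in EPO, oxidative-stress markers and immune parameters. As secondary results it lists patient-reported outcomes, stress reduction and psychological well-being. Cognition is in neither list, so objective 2 promises something that the article's own account of its results does not deliver.

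**The case against.** The strongest reply is that the harm is hypothetical. Section 3 does not list cognition among the outcomes to be reported, section 2.8.2 labels the analytes correctly, and the aims in the abstract and at the end of the rationale speak of psychological well-being. On this view the word is a slip in two sentences of the introduction. Sample size, which is tied to an erythropoiesis measure such as EPO, is unaffected, as are randomization, the visit schedule and the analysis methods.

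Much of this stands, and it limits the point. A reader might infer that the trial will announce a marker difference as a cognitive benefit; section 3 does not support that inference. A reader might infer that objective 2 has no endpoint at all; only its cognitive part lacks one. A reader might take the words "further suggest benefits for cognitive and emotional function" in section 5 as a planned conclusion. The sentence is about a possible mechanism, written before any data exist, and does not say what the trial will conclude. A reader might also assume that the analytes are blood or serum levels. The article says only that a clinical specimen is used for them, and the argument does not depend on which.

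What does not stand is the idea that nothing needs changing. The two sentences are a primary objective and a statement that the effect is quantified in a specimen. They define what the trial may claim, and they disagree with sections 2.8.2 and 3. The secondary objective's questionnaire list is formally open, but sections 2.9.1 to 2.9.3 and section 3 name the same three instruments, and objective 2 names its own measures in any case. Section 4 suggests that oxygen therapy might influence neurotransmitters. That is a hypothesis about mechanism and does not validate these analytes as a measure of cognition.

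It can also be said that the sponsor might prefer to add a validated cognitive measure. That would be a legitimate alternative, but it means new assessments rather than a correction of wording.

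**Conclusion.** The point holds for the cognitive part of primary objective 2, which has no valid endpoint at any visit. As written, the objective sets up a question that the data cannot answer in either direction.

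The size is one component of one of four primary objectives. There is no effect on error rates, on the 127 patients per group, or on the other objectives. The correction should be made because it concerns a primary-level claim and costs almost nothing.

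The conclusion rests on two assumptions: that the packages in sections 2.8 and 2.9 and Table 1 are the complete set of outcome assessments, and that the markers are not established measures of cognition. The article offers no evidence that they are.

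**What to change.** Reword objective 2 as the effect of NBO on oxidative-stress, stress-hormone and neurotransmitter markers and on allostatic load. Remove cognition from that objective and from the sentence about the clinical specimen, so that both agree with sections 2.8.2 and 3. State that emotional function is assessed by HADS and PSQ, which are already collected as secondary outcomes.

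The change is to wording only, with no new data, visits or patients. Section 3 schedules the first enrollment for March 2026, after the article's publication in July 2025, so on that timetable the change could be made before any patient entered. The one thing given up is a primary-level claim on cognition that the planned data could not have supported.
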